#### Anthropometric measurements

Anthropometric measurements will be collected by using standardised equipment and examination procedures. The weight and height of the participants will be measured while they are wearing light clothes and no shoes in the morning of the follow-up. Body fat percentage and total body water will be calculated by using a one-stop self-service monitoring machine (E-Techco Information Technologies Co., Shenzhen, China). WC will be measured at the midpoint between the lower edge of the rib arch and the iliac crest while the subjects are standing and breathing steadily. The hip circumference (HC) will be measured at the widest part of the buttocks at the intertrochanteric level to the nearest 0.1 cm. The other anthropometric indexes will be calculated by using the following equations: body mass index (BMI) = weight/height (kg/m^2^), waist-to-hip ratio (WHR) = waist/hip (m/m), and waist-to-height ratio (WHtR) = waist/height (m/m). Blood pressure (BP) will be measured by using a standard mercury sphygmomanometer with a cuff placed on the upper right arm after a 5-min rest with 1-min intervals before subsequent measurements. Three BP readings will be recorded, and the mean will be calculated. All anthropometric measures will be taken by trained research assistants using standard equipment in accordance with standard guidelines. A list of anthropometric measurements is presented in Table 2.

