### Study procedures

#### Recruitment and screening

Table 1 provides the schedule for enrolment, intervention and follow-up. Participants will be recruited by placing advertisements on social media sites and community bulletin boards. Once a volunteer expresses initial interest in participating in the study, he or she will have face-to-face or telephone communication with the research assistant. Detailed information on the study trial, including the purpose, the methods of the intervention and duration, will be provided to the volunteers. If they are still interested in this project after careful consideration, the structured standardised screening questionnaire, which is based mainly on the inclusion and exclusion criteria for the study, will be used to assess the potential eligibility of the participants for the study. Potential participants who are found not to be eligible will be excluded at this stage. Eligible participants will be invited to attend a further screening visit, which will take place at the CHSC. First, informed consent will be obtained from all participants. Second, for safety assessments, liver and renal function will be evaluated by collecting fasting blood samples and spot urine samples. Third, the anthropometric index will be measured by the trained investigators.

**Table 1 Tab1:** Schedule for screening, intervention and follow-up (test visit)

	Screening (−4 week)	Test visit 1 (week 0)	Test visit 2 (week 6)	Test visit 3 (week 12)
Screening questionnaire	X			
Demographic data	X			
Medication, health status and any changes	X	X	X	X
Informed consent	X			
Height and weight	X	X	X	X
Waist circumference and hip circumference	X	X	X	X
Body composition (bioelectric impedance)	X	X	X	X
Blood pressure	X	X	X	X
Blood sample	X	X	X	X
Allocation		X		
Physical activity questionnaire		X	X	X
Mini-mental State Examination		X		X
24-h diet recall		X	X	X
Spot urine sample	X	X		X
Faecal sample		X		X
Provided supply of capsules		X	X	
Tablet count			X	X
Compliance assessment			X	X
Assess adverse reactions			X	X
Collect unused test product			X	X

**Table 2 Tab2:** Biological and anthropometric parameters analysed in the lutein supplementation study

	Variable	Screening (−4 week)	Test visit 1 (week 0)	Intermediate visit (week 6)	Test visit 2 (week 12)
Biological	TC	X	X	X	X
	TGs	X	X	X	X
	HDL-C	X	X	X	X
	LDL-C	X	X	X	X
	ALT	X	X	X	X
	AST	X	X	X	X
	Creatinine	X	X	X	X
	FBG	X	X	X	X
	Insulin	X	X	X	X
	Lutein	X	X	X	X
	RBP4		X		X
	Adiponectin		X		X
	IL-6		X		X

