#### Test visit

At test visit 1 (week 0), eligible participants will be allocated to either a lutein supplement group or a control group. The lutein supplement group will take one 10 mg lutein capsule daily, and the control group will take the placebo. Participants will be given a 6-week supply of capsules at both visit 1 and visit 2 and will be required to return the remaining capsules at the next visit, which will be counted and recorded for each participant to ensure compliance with the protocol. Participants will be defined as non-compliant if they took less than 80% of the study product. Medication, health status or any recent changes around the inclusion and exclusion criteria since the completion of the screening questionnaires will also be re-assessed to evaluate whether participants are still suitable to participate in the study. Anthropometric measurements, dietary assessments and blood samples will be collected at each visit, and stool samples and spot urine samples will be collected at test visit 1 and test visit 3. At test visit 1 and test visit 3, the volunteers will be asked to complete the short form of the International Physical Activity Questionnaire (IPAQ-short form) and the Mini-mental State Examination (MMSE). At the end of each visit, participants will be thanked for their time and will be provided with breakfast. After test visit 3, people in the placebo group will be given the same amount of lutein supplements as that provided to the intervention group. The full details of the data that will be collected at each time point can be found in Table 1.

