#### Study outcomes

The primary outcome consists of changes in the inflammatory biomarkers between the intervention and placebo group from baseline (test visit 1) to 12 weeks later (test visit 2). The secondary objectives are to assess changes in the anthropometric indexes, including weight, WC, HC and body composition.

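### The BMI equation lacks the square on height, and height is re-measured at every visit with no single height fixed for BMI and WHtR: correct the notation and use one baseline height per participant

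*Protocol article*

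**What the plan says.** All references are to the protocol article.

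- **Anthropometric measurements**, BMI equation: "body mass index (BMI) = weight/height (kg/m^2". The same sentence gives "waist-to-height ratio (WHtR) = waist/height (m/m", where equation and unit agree.
- **Anthropometric measurements**, procedure: "The weight and height of the participants will be measured while they are wearing light clothes and no shoes in the morning of the follow-up".
- **Test visit**: "Anthropometric measurements, dietary assessments and blood samples will be collected at each visit".
- **Table 1**: the row "Height and weight" is marked at screening and at weeks 0, 6 and 12.
- **Table 2**: BMI and WHtR are marked at the same four time points.
- **Study outcomes**: "The secondary objectives are to assess changes in the anthropometric indexes, including weight, WC, HC and body composition". BMI and WHtR are not in that list, although Anthropometric measurements counts both among the anthropometric indexes.

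No section says which height reading enters BMI or WHtR at weeks 6 and 12.

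**The concern.** There are two separate matters.

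The first is notation. Weight divided by height has the unit kg/m. The printed unit, kg/m², requires height squared, so the expression contradicts itself.

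The second is how the index is formed. If the height read at each visit goes into that visit's BMI and WHtR, then any difference between a participant's week-0 and week-12 heights enters the change. In adults over 12 weeks that difference is reading error. Because BMI uses the square of height, a given relative error in height becomes about twice that relative error in BMI. The added noise carries no information about lutein and can be avoided entirely. What is at stake is a modest loss of precision for change in BMI, and less for WHtR.

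**Working it through.** The protocol gives no SD, effect size or power for BMI or WHtR, so there is no figure of its own to reproduce. Every SD below is an assumption.

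**1. Equation against unit.** Take 75 kg and 1.65 m (assumed).
- Weight/height: 75/1.65 = 45.5 kg/m.
- Weight/height²: 75/1.65² = 27.5 kg/m².

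Only the second has the printed unit.

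**2. Noise added to BMI change.** Let e be the SD of a height reading, with independent errors at the two visits. The error SD of BMI at one visit is 2 × BMI × e/height. For the difference of two visits, multiply by √2. With BMI 29 and height 165 cm:
- e = 0.3 cm: √2 × 2 × 29 × 0.3/165 = 0.149 kg/m²
- e = 0.5 cm: 0.249 kg/m²
- e = 1.0 cm: 0.497 kg/m²

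**3. SD of BMI change with one fixed height.** This is the weight-change SD divided by 1.65² = 2.7225:
- 1.5 kg: 0.551 kg/m²
- 2 kg: 0.735 kg/m²
- 3 kg: 1.102 kg/m²

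**4. Variance inflation**, (step 2/step 3)²:

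| Height-reading SD | Weight-change SD 1.5 kg | 2 kg | 3 kg |
|---|---|---|---|
| 0.3 cm | 7% | 4% | 2% |
| 0.5 cm | 20% | 11% | 5% |
| 1.0 cm | 81% | 46% | 20% |

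**5. A second set of assumptions.** With BMI 27.5, height 165 cm and a BMI-change SD of 0.8, the inflation is 3.1%, 8.7% and 34.7% for 0.3, 0.5 and 1.0 cm. With 52 per arm, a comparison that would have 80% power falls to 78.8%, 76.7% and 67.5%. The order of magnitude is the same. These powers only illustrate the scale, since the trial was not sized for BMI.

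**6. 12-week value without baseline adjustment.** Only one height error enters: 2 × 27.5 × e/165 = 0.100, 0.167 and 0.333 kg/m². Against an assumed between-person SD of 3 kg/m², the variance rises by 0.1%, 0.3% and 1.2%.

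**7. WHtR.** Height enters once, so the relative error is half that in BMI. For a 90 cm waist (the eligibility minimum for men) and e = 0.5 cm, the noise is equivalent to √2 × 90 × 0.5/165 = 0.39 cm of waist change. To match the 11% found for BMI (SD ratio 0.249/0.735 = 0.338), the SD of waist change would have to be as small as 0.39/0.338 ≈ 1.1 cm. Any larger SD gives less inflation.

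**The case against.** The opposing case has five parts.

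- **The missing square will mislead nobody.** This stands. The name, the unit and the conventional use of BMI in the Discussion (a threshold in kg/m²) all identify ordinary BMI. A reader might infer that values in the forties will be analysed as BMI. The documents do not support that: they support only a correction of notation.
- **The protocol does not say that same-visit height is used.** Literally true. Measuring height again does not oblige anyone to divide by the new reading, and an article may leave such derivations to a fuller document. But the article does schedule the later readings, lists both indexes at the same visits and prints height in both equations. If one height were used throughout, the week-6 and week-12 readings would have no stated use. Same-visit height is therefore the plain reading, though not an explicit statement.
- **BMI change is not a named endpoint.** This stands. The Study outcomes list names weight, WC, HC and body composition, so BMI and WHtR come in only through the general term. Weight, WC and HC do not use height, and neither do the primary inflammatory biomarkers or the triglyceride-based sample size.
- **The magnitude is assumed and usually small.** This stands. The protocol specifies standardised equipment, trained staff, no shoes and morning measurement, which makes a 1.0 cm reading SD, and the large inflations that go with it, a pessimistic case. The planned analysis of covariance compares arms at 12 weeks and names only age and sex as example covariates. If baseline BMI is left out, the noise is negligible (step 6).
- **Repeat readings can serve as a data check.** This is fair, so dropping them should be optional.

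**Conclusion.** The point holds as a minor one with two parts. The equation is wrong as printed and needs an exponent. The schedule, read plainly, builds avoidable height-reading error into BMI and WHtR change. For BMI change the variance cost is about 4% to 11% at a reading SD of 0.3 to 0.5 cm, assuming BMI 29, height 165 cm and a weight-change SD of 2 kg. It is larger if weight change varies less or height is read less carefully, and smaller in the opposite case. The figures apply to change from baseline or to a closely equivalent baseline-adjusted analysis.

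A reader might go on to infer that the BMI comparison will be biased, or that a stated secondary endpoint is compromised. The documents do not support either. Under double-blind allocation the reading error is unrelated to arm, so it leaves the expected difference and the type I error unaffected. BMI is at most implied among the secondary measures, and no power rests on it.

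**What to change.** - Write BMI = weight (kg)/height² (m²).
- State that BMI and WHtR at every visit are computed from one baseline height per participant: either the week-0 reading or the mean of the screening and week-0 readings.

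The cost is one line of text. It can be applied to data already collected, because it changes only how the indexes are derived. The week-6 and week-12 height readings are then not needed for these indexes. They may be dropped, saving two measurements per participant, or kept as a data check.

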#### Biological sampling

At baseline and the middle and end of the trial, 12 mL of venous blood sample (4 mL in EDTA-coated sterile tubes and 8 mL in regular tubes) will be collected after the participants fast overnight. Table 2 summarises all the blood markers that are examined during the study. In addition to the indexes of liver and renal function (alanine aminotransferase (ALT), AST and creatinine), blood glucose, insulin, the lipid profile (TC, TGs, high-density lipoprotein cholesterol (HDL-C) and LDL-C) and CRP will be tested on the day of blood collection. Enzymatic methods (Biosino Biotechnology Company Ltd., Beijing, China) will be used for measuring serum hepatic enzymes, including ALT and AST. Serum creatinine will be determined by using the Jaffe method. Insulin concentrations (μU/mL) will be measured with a chemiluminescence microparticle immunoassay, high-sensitive CRP will be measured by using the immunoturbidimetry assay, and fasting blood glucose (mmol/L) will be measured by using the enzymatic colorimetric method with glucose oxidase using a commercially available kit. IR will be estimated by the homeostasis model assessment of insulin resistance (HOMA-IR): fasting insulin (μU/mL)*(fasting glucose (mmol/L)/22.5) [24]. The lipid profile will be determined by colorimetric methods using commercial kits (Biosino Biotechnology Company Ltd.) in a Hitachi 7080 automated analyser (Hitachi, Ltd., Tokyo, Japan). Serum lutein (μmol/L) will be analysed by high-performance liquid chromatography-tandem mass spectrometry. Retinol-binding protein 4 (RBP4) (μg/mL) and adiponectin (μg/mL) will be measured by using an enzyme-linked immunosorbent assay (ELISA) kit (Adipogen, San Diego, CA, USA). Serum levels of MCP-1, TNF-α, IL-6 and IL-1β will be measured by using the flow cytometry method (FCM).

Participants will be required to provide spot urine samples on the day of the screening and at test visit 1 and test visit 3. A routine urine test will be performed on the day of collection. Faecal samples will be collected at test visit 1 and visit 3 using a stool specimen collection kit, which includes the operating instructions, an ice pack, gloves, one sterile container and spoon, a sealed plastic pouch and a cool box. Participants will collect their faecal samples and bring them to the CHSC and then the samples will be transported and stored for further analysis.

A research biobank, where blood, urine and faecal samples will be stored with an identification number for later analysis of biomarkers, will be established in relation to this trial. Participants will be informed about the research biobank before signing the informed consent form. Only investigators and the research team will retain the right to access the relevant data.

#### Dietary assessments

At the screening periods, eligible participants will complete a questionnaire on food intake, which captures information on how many servings of vegetables rich in lutein they consume, including sweet potato leaves, spinach, broccoli, collards, leeks and lettuce. This questionnaire provides a reference to roughly evaluate dietary lutein intake. At each test visit, individuals will be required to provide 3 days of 24-h diet recall via the phone or the internet. The data will be collected and calculated by a professional nutritionist in accordance with the Chinese Food Composition Database (2009) and the US Department of Agriculture Nutrients Database [28, 29]. At each follow-up, questions on whether the participants have changed their diets will be asked, including questions regarding a significant reduction or increase in dietary intake.

#### Study outcomes

The primary outcome consists of changes in the inflammatory biomarkers between the intervention and placebo group from baseline (test visit 1) to 12 weeks later (test visit 2). The secondary objectives are to assess changes in the anthropometric indexes, including weight, WC, HC and body composition.

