### Study participants and eligibility criteria

It is estimated that 52 participants per treatment group would be required for 80% power and a 5% level of significance to detect the change in serum TGs over 12 weeks of supplementation [27]. Allowing for a dropout rate of about 15%, we aim to recruit 120 participants in total. Participants were eligible for this study if they fulfilled the following criteria: (1) age between 18 and 60 years, (2) waist circumference (WC) of at least 90 cm for males and at least 85 cm for females, (3) deficient lutein intake (dietary lutein intake of less than 10 mg/d), and (4) willingness to sign the informed consent form. People meeting any of the following criteria will be excluded from participation: (1) use of lutein supplementation or related health-care products within 1 month, (2) use of antibiotics within 1 month, (3) secondary obesity, (4) adoption of a special diet or meal replacement in the previous 2 weeks, (5) use of insulin or insulin sensitizers within 1 month, (6) chronic diseases (including type 2 diabetes, hypertension and dyslipidaemia) for over 10 years, (7) hepatorenal dysfunction (creatinine of more than 1.2 times the upper normal limit of creatinine, aspartate aminotransferase (AST) of more than 1 time the upper normal limit), (8) any active tumours/cancers, (9) regular use of drugs affecting blood lipid, (10) pregnancy or lactation or (11) history of gastrointestinal surgical operation.

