### Statistical analysis

Two populations will be used in the analyses. The intention-to-treat (ITT) population will include all participants who have been randomly assigned, whereas the per-protocol (PP) population will include all participants who accomplish the entire intervention. The baseline characteristics of the study will be summarised as the means ± standard deviations for parametrically distributed data, geometric mean values (and 95% confidence intervals) for non-parametrically distributed data, and numbers (percentages) for categorical data.

Differences between participants who complete and withdraw from the trial will be analysed by using an independent *t* test or the Mann–Whitney test for continuous variables (e.g., age) and the chi-squared test for categorical variables (e.g., sex). For primary and secondary outcomes, analysis of covariance will be used to examine differences between lutein supplement and placebo at 12 weeks, adjusting for potential confounding factors and effect modifiers (e.g., baseline age and sex). The present study has no plan for subgroup analysis. Our statistical analysis will be performed by using R software, and the results will be considered significant at a *P* value of less than 0.05.

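### The primary outcome is an unnamed set of inflammatory biomarkers judged at P < 0.05 with no rule for combining them; if any one marker suffices, the false-positive chance is about 13–23%, not 5%

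*Protocol article*

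**What the plan says.** All references are to the protocol article.

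- **Study outcomes:** "The primary outcome consists of changes in the inflammatory biomarkers between the intervention and placebo group from baseline" to 12 weeks. The set is plural. No lead marker, composite or order is given.
- **Biological sampling:** "Serum levels of MCP-1, TNF-α, IL-6 and IL-1β will be measured by using the flow cytometry method (FCM"), and "high-sensitive CRP will be measured by using the immunoturbidimetry assay". Table 2 schedules all five at weeks 0 and 12. Two further proteins follow the same schedule: "Retinol-binding protein 4 (RBP4) (μg/mL) and adiponectin (μg/mL) will be measured by using an enzyme-linked immunosorbent assay (ELISA) kit".
- **Statistical analysis:** "For primary and secondary outcomes, analysis of covariance will be used to examine differences between lutein supplement and placebo at 12 weeks", and "the results will be considered significant at a *P* value of less than 0.05". The same section says "Two populations will be used in the analyses", meaning ITT and per-protocol (PP), without saying which leads.
- **Study participants and eligibility criteria:** the sample size statement reads: "It is estimated that 52 participants per treatment group would be required for 80% power and a 5% level of significance". The variable behind that calculation is the change in serum triglycerides, which is not an inflammatory biomarker.

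**The concern.** Which variable, or which closed list of variables, carries the trial's main claim belongs in the protocol. Here the list is open, and the one threshold stated applies to results singly. A reader of the eventual paper could not tell whether one significant cytokine out of five was the planned criterion for success or was picked out afterwards.

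Two things are at stake. The first is the type I error of the claim that lutein changes inflammation, which the stated rule does not hold at 5% if a single significant marker is enough. The second is the edge of the family. The Introduction lists adiponectin with IL-6 and TNF-α as adipokines, so someone could argue it in or out once results are known. The sample size section does not point to a lead marker, because it is built on triglycerides.

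**Working it through.** **Inputs.** Five markers (Biological sampling; Table 2). Threshold 0.05 (Statistical analysis), taken as two-sided because sidedness is not stated. 52 per group, 80% power, 5% significance, about 15% dropout and 120 recruited (Study participants and eligibility criteria). The document gives no correlations between markers, so those below are assumptions.

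**Step 1: the plan's own figure.** 2 × 52 = 104 evaluable. Multiplying up, 104 × 1.15 = 119.6, which rounds to the stated 120. Dividing by the retained fraction, 104 / 0.85 = 122.4, or 123. The 120 is reproduced closely enough. The 52 per group cannot be rebuilt, because no difference or SD is given.

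**Step 2: five independent null markers, any one counted as success.** P(at least one P < 0.05) = 1 − 0.95^5 = 1 − 0.774 = 22.6%.

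**Step 3: correlated markers.** Equicorrelated normal test statistics, five tests, two-sided critical value 1.96:

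| Assumed correlation | At least one false positive |
|---|---|
| 0 | 22.6% |
| 0.3 | 20.9% |
| 0.4 | 19.7% |
| 0.5 | 18.3% |
| 0.7 | 14.8% |
| 0.8 | 12.7% |

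**Step 4: false benefit only.** Counting only the beneficial direction, with 2.5% per marker: 1 − 0.975^5 = 11.9% if independent, 10.5% at correlation 0.3 and 9.1% at 0.5. The nominal figure to compare with these is 2.5%.

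**Step 5: what an adjustment achieves.** At 0.05 / 5 = 0.01 per test, the family-wise error under independence is 1 − 0.99^5 = 4.9%. Holm starts at that step and is less strict afterwards, while still keeping the overall error at or below 5%.

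**Step 6: power, as an assumption only.** The standardised difference that 52 per group detects with 80% power at two-sided 5% is (1.960 + 0.842) × √(2/52) = 0.549. If a marker had that effect, the noncentrality would be 0.549 × √(52/2) = 2.80. Power at 0.01 would then be Φ(2.80 − 2.576) = 59% by the normal approximation, or 57% with the t distribution. Nothing in the document shows that the triglyceride effect carries over to a marker.

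**The case against.** The strongest reply is that the document never says one significant marker is enough. It states a single hypothesis about inflammatory and metabolic factors and no success rule. A rule that all markers must be significant would not inflate the error at all. That stands: a reader might infer that the plan runs a false-positive risk of about 20% as a fact, and the text supports this only under an any-one-marker rule. The percentage is therefore conditional here. The absence of a rule does not rescue the plan, because it leaves the criterion open until results are seen.

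A second reply is that this is a journal article and the analysis plan may hold the multiplicity method. Detail of that kind is fairly left to such a plan. The identity of the primary variable is not, and the article is not silent on significance: it states a threshold and no adjustment.

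Third, the range matters. Correlations are unknown, high ones bring the figure down to about 13%, and two-sided counting includes apparent harm. Both are allowed for above.

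Two stronger readings are not supported:

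- **Seven markers.** Adding adiponectin and RBP4 gives 1 − 0.95^7 = 30.2% under independence. But the document never calls RBP4 inflammatory, so that count is a reader's own grouping.
- **Success in either ITT or PP.** A reader might add this as a further source of error. The article lists both populations but does not say that a PP-only result would count, and any figure would need an assumed correlation between the two analyses.

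**Conclusion.** The point holds in conditional form. The primary outcome is an unnamed, unranked set of at least five inflammatory biomarkers, and the only stated decision rule is an unadjusted 0.05. If one significant marker is read as a positive primary result, the type I error of the main claim is about 13–23% rather than 5% over assumed correlations of 0.8 down to 0. This rests on five markers, two-sided tests, equal correlations and the any-one rule, which the document neither states nor excludes. The defect needs correcting because it concerns the definition of the main claim.

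**What to change.** Before unblinding, adopt one of two texts:

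1. Name one inflammatory marker as the single primary outcome, tested at two-sided 5% in the ITT population, with the other markers secondary.
2. List CRP, IL-6, IL-1β, MCP-1 and TNF-α as the primary family and apply Holm across the five at overall two-sided 5% in the ITT population.

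Under either text, make PP supportive and any marker outside the list, such as adiponectin or RBP4, secondary. A stated all-markers rule would also control the error, but it asks for significance on all five.

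The change takes a few sentences and needs no extra participants, visits or assays. Trial status says recruitment is still open, and Randomisation and blinding keeps allocation concealed until data collection ends, so there is time to make it.

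The cost of the second text is lower power per marker. Its size cannot be derived from the document. If the implied standardised difference of about 0.55 applied to a marker, power at the strictest 1% step would be about 57–59% rather than 80%. The first text avoids this multiplicity cost, although power for any inflammatory marker remains unestablished because the sample size was planned on triglycerides.
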